### Confidentiality {27}

Identifying information will be removed and substituted by an unique study number. Nonetheless, a randomisation list will be remained with the name linked to the study number. The randomisation list will be securely stored by the local investigator and is only available for the study team and on request for the monitor, data safety monitoring board and the pharmacy. After the trial, the data will be stored secured at the secured long storage of the UMCG until it is deemed appropriate to be destroyed.

### Plans for collection, laboratory evaluation, and storage of biological specimens for genetic or molecular analysis in this trial {33}

The pulmonary inflammatory response is measured in non-bronchoscopic wedged broncho-alveolar lavage (BAL) fluids and the systemic inflammatory response in plasma samples [38]. Measurement of pro-inflammatory cytokines and chemokines will be done using Luminex bead technology. Blood samples and BAL fluid are pre-processed and stored per specific standard operating procedures at the participating sites. Full analysis of the samples will be coordinated by the UMCG.

## Statistical methods

### Statistical methods for primary and secondary outcomes {20a}

Data is analysed with an intention-to-treat approach. The primary outcome measure is a continuous outcome parameter. First, it will be tested for normality using the Shapiro-Wilk test. Dependent upon the outcome of this test, in the univariate analysis, the primary outcome will be displayed as mean ± standard deviation or median (25–75 interquartile range) and analysed using either the Student *t* test or the Mann-Whitney *U* test. Paired analysis will be used to compare the primary outcome with its baseline value. In multivariate analysis, zero inflated regression analysis is used to adjust for possible confounding by age, gestational age, family history of asthma and/or allergy, season in which questionnaire was filled out, parental smoking, and parental perception of the outcome of randomisation. Depending on the outcome of the analysis on randomisation outcome, variables that were significantly different between the intervention and control arm will also be adjusted for in the multivariate analysis. On top of that, we will adjust if there is an imbalance in the use of (non-) pulmonary specific ancillary treatment used during PICU admission.

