### Outcomes {12}

#### Primary outcome measure

Cumulative respiratory morbidity score 12 months after PICU discharge, adjusted for confounding by age, gestational age, family history of asthma and/or allergy, season in which questionnaire was filled out, day-care and parental smoking.

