### Sample size {14}

The primary outcome is the cumulative respiratory morbidity score 12 months after PICU discharge. A classical sample size based on a independent sample *t* test between two groups was calculated, assuming a 20% difference in cumulative mean respiratory morbidity score. This resulted in a required sample size of 148 patients (*N* = 74 intervention versus *N* = 74 placebo) to demonstrate a 20% reduction in respiratory symptoms in the intervention group compared to the placebo with an alpha of 5% and power of 80%. Considering a potential maximum drop-out of 20% per group because of withdrawal of consent or loss to follow-up, we need to enrol *N* = 89 patients per group. Thus, the total sample size is 178 patients.

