## Data collection and management and storage of biological specimens

### Plans for assessment and collection of outcomes {18a}

#### Primary outcome

The respiratory morbidity will be assessed using a structured questionnaire in agreement with recommendations from the American Thoracic Society [29]. This parental questionnaire studies the presence of respiratory symptoms including cough, wheezing and shortness of breath during rest and/or activity. The questionnaire consists of 14 items that can only be answered by yes or no. The questionnaire is commonly used and validity of the items in the respiratory morbidity score has been shown [29, 30]. Upon discharge, parents or legal caretakers are asked for their e-mail address and phone number; the personalised link to the web-based questionnaire will be e-mailed to them 12 months after PICU discharge. If there is no response within 7 days, they will receive a reminder via e-mail. The questionnaire is personalised and anonymised. The same questionnaire is used upon PICU admission to study baseline respiratory morbidity.

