### Methods in analysis to handle protocol non-adherence and any statistical methods to handle missing data {20c}

All study participants who have received a dose of the study drug will be included in a modified intention to treat analysis. Participants who have received the study drug during 48 h and with a respiratory morbidity score 12 months after discharge (primary outcome measure) will be included in the per-protocol population.

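### The primary analysis contradicts itself on test, covariates and population, and would usually not test the 20% mean difference that was powered

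*Protocol article*

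**What the plan says.** **Hypothesis and power.** Sample size {14} uses an independent-samples t test, "assuming a 20% difference in cumulative mean respiratory morbidity score", "with an alpha of 5% and power of 80"%. "This resulted in a required sample size of 148 patients", 74 per arm. No mean or SD is printed.

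**Endpoint.** The Abstract and the primary outcome measure under Outcomes {12} define the endpoint as the 12-month score after adjustment. The list of adjusters ends with "season in which questionnaire was filled out, day-care and parental smoking".

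**Score.** Under Plans for assessment and collection of outcomes {18a}: "The questionnaire consists of 14 items that can only be answered by yes or no".

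**Analysis.** Statistical methods {20a} classes the score as continuous. "First, it will be tested for normality using the Shapiro-Wilk test"; the result decides between Student's t test and Mann-Whitney for the unadjusted comparison. A paired comparison with baseline follows. Then: "In multivariate analysis, zero inflated regression analysis is used to adjust for possible confounding by age, gestational age" and further variables. That list omits day-care and includes what the parents believe the allocation was. Two conditional additions follow: variables that differ significantly between the arms, and ancillary treatment given in the PICU if its use is imbalanced.

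**Population.** Section {20a} opens with intention-to-treat. Section {20c} says: "All study participants who have received a dose of the study drug will be included in a modified intention to treat analysis", and also defines a per-protocol set. Neither section names the primary set.

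**The concern.** The trial has one stated hypothesis, a 20% lower mean score. At least three analyses could answer it (t test or Mann-Whitney, and a zero-inflated regression), run on any of three populations with either of two covariate lists. They estimate different things and can disagree. No sentence says which one decides the trial. Interim analyses {21b} allow stopping for futility on the same primary outcome, so the ambiguity also reaches the data safety monitoring board.

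Two features affect validity as well as clarity. Parents can form a belief about allocation only after randomisation. Ancillary treatment in the PICU is also given after randomisation and may respond to the study drug. Adjusting for either can bias the treatment effect. Adding covariates because they differ significantly between arms makes the model depend on the data.

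**Working it through.** **1. What the sample size implies.** Inputs from Sample size {14}: 74 per arm, power 80%, alpha 5% (sidedness is not stated; two-sided assumed), relative difference 0.20.
- Solving the t-test power equation for n = 74 gives d = 0.464.
- d = 0.20 × mean / SD, so SD/mean = 0.20 / 0.464 = 0.431. One-sided, d = 0.411 and SD/mean = 0.49.
- At SD/mean = 0.43 the t-test formula returns 74 per arm. The figure is internally possible, but it cannot be reproduced independently because no mean or SD is given.

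**2. Sensitivity of power.** Normal approximation: power = Φ(0.20/(SD/mean) × √(74/2) − 1.96). SD/mean is an assumed range.

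| SD/mean | Power at 74 per arm | Needed per arm for 80% |
|---|---|---|
| 0.43 | 81% | 73 (74 with the t distribution) |
| 0.50 | 68% | 99 |
| 0.75 | 37% | 221 |

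Some zero inflation is compatible with the plan. Take 10% excess zeros and a binomial(14) score with mean 7 in the rest. The mean is 0.9 × 7 = 6.3. The variance is 0.9 × 3.5 + 0.9 × 0.1 × 49 = 7.56, so SD = 2.75 and SD/mean = 2.75/6.3 = 0.44.

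**3. How often the t test is reached.** Assumptions: one point per item (range 0-14), 74 per arm, beta-binomial scores with or without excess zeros, 2,000 simulated trials per setting, Shapiro-Wilk on the pooled sample.
- Symmetric score (mean 7, SD/mean 0.43, no excess zeros): normality is rejected in about 89% of trials with no effect and 95% with a 20% effect. The spread over repeated runs was 86-97%.
- Skewed or zero-inflated scores: rejected in 100%.

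Mann-Whitney would therefore usually be used. It compares distributions by rank and does not estimate a difference or ratio of means.

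**4. Does the choice of test matter?** Simulated power for a 20% lower mean:

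| Assumed score (overall mean) | t test | Mann-Whitney |
|---|---|---|
| Mean 7, SD/mean 0.43, no excess zeros | 80% | 80% |
| Mean 7, SD/mean 0.43, 10% excess zeros | 84% | 95% |
| Mean 3, SD/mean 1.0, 30% excess zeros | 25% | 18% |

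With no treatment effect, the two-stage procedure rejected in 3.8-5.4% of trials.

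**5. One mean reduction, several zero-inflated results.** The mean is (1 − π) × μ, where π is the excess-zero share and μ the count mean. With π = 0.30 in controls and a 20% lower mean, count ratio = 0.8 × 0.70 / (1 − π in treated).
- π treated 0.30: count ratio 0.80, zero-part odds ratio 1.00.
- π treated 0.37: 0.56/0.63 = 0.89, odds ratio 1.37.
- π treated 0.44: 0.56/0.56 = 1.00, odds ratio (0.44/0.56)/(0.30/0.70) = 1.83.

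In the last case the count part shows nothing, although the hypothesised effect is fully present.

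**6. The passages side by side.**

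| Item | Abstract and Outcomes {12} | {20a} | {20c} |
|---|---|---|---|
| Day-care | adjusted | absent | – |
| Parental perception of allocation | absent | adjusted | – |
| Arm-difference and ancillary-treatment covariates | absent | conditional | – |
| Population | – | intention-to-treat | dosed children, plus per-protocol |

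**The case against.** The strongest reply is that the article can be read coherently. The endpoint is defined as the adjusted score and {20a} labels the t test or Mann-Whitney step univariate, so the adjusted regression is the natural primary analysis. Model family and reporting scale are commonly left to the analysis plan, and a zero-inflated fit can be summarised as a ratio of marginal means. This has weight, but it leaves the conflicting covariate lists, the post-randomisation adjusters and the conflicting populations in place. The regression read as primary is also not the test that was powered.

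Four stronger readings are tempting, and the documents do not support them.
- A reader might infer that the 20% mean difference is never tested. The Student t branch in {20a} is exactly the powered test; it is only unlikely to be reached, and it is unadjusted.
- A reader might infer that the implied SD rules out a zero-inflated score. The 10% example gives SD/mean of 0.44, close to the required 0.43.
- A reader might take low power as established. With 20-30% excess zeros and a mean of 5 in the rest, t-test power would be 30-47%, but that is one end of an assumed range.
- A reader might think the normality gate inflates the type I error or lets a result be picked. It is a rule fixed in advance, and simulated error stayed at 3.8-5.4%. The valid objection is that the quantity being tested changes with the outcome of the gate.

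The number of children randomised but never dosed is unknown, so the size of the population conflict cannot be shown.

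**Conclusion.** The concern holds as a set of printed contradictions and poor choices. The deciding analysis is not named. The powered comparison of means would usually be replaced by a rank test in the unadjusted analysis. The zero-inflated model is not reduced to one effect. The covariate lists disagree and admit post-randomisation variables. Two intention-to-treat definitions coexist. Following {20a} as written can give conflicting primary results and a biased adjusted effect.

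The rejection rates and the power range rest on assumptions: one point per item, a single 12-month questionnaire, two-sided 5%, and distributions of my choosing. No scoring rule is printed, and cumulative is not defined; it could mean a sum over several questionnaires. The contradictions between sections do not depend on any of these assumptions.

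**What to change.** - Delete the Shapiro-Wilk step.
- Name one primary analysis of the difference or ratio of mean 12-month scores. Examples are a log-link model with robust standard errors, or the marginal mean ratio from the zero-inflated model.
- Analyse all randomised children, and state a rule for those without a 12-month score, including those who die before it is due.
- Use one covariate list in the Abstract, Outcomes {12} and {20a}. Limit it to baseline variables plus season of questionnaire. Season is known only at follow-up, but treatment is unlikely to affect it.
- Remove parental perception, covariates selected by significance, and ancillary treatment from the primary model.
- Keep Mann-Whitney and the separate zero-inflated components as supportive analyses, and label the dosed and per-protocol sets the same way.
- Print the mean and SD behind 74 per arm. Check SD/mean of about 0.43 on blinded pooled scores, and restate power if it differs.

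The cost is wording in the protocol and analysis plan, a small blinded calculation, and possibly a less favourable stated power. It should be done before unblinding.

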#### Secondary outcome measures

Secondary outcomes include LCI and FRC measured using multiple breath wash-out 12 months after PICU discharge, and the level and time course of the cumulative respiratory morbidity score assessed at baseline, 3, 6 and 9 months after PICU discharge. Secondary outcome measures related to the acute phase of disease (i.e., during PICU admission) include level and time course of ventilator settings (peak inspiratory pressure, plateau pressure, mean airway pressure, driving pressure, PEEP, set rate, total rate, inspiratory time), respiratory system mechanics (quasistatic compliance, dynamic compliance, respiratory system resistance), metrics of oxygenation (SpO_2_/FiO_2_ ratio, PaO_2_/FiO_2_ ratio, OI, OSI) and ventilation (PCO_2_, pH), and hemodynamic parameters (heart rate, blood pressure, central venous pressure, daily cumulative fluid balance, number of fluid challenges). We will measure the level and time course of the non-respiratory pediatric logistic organ dysfunction 2 (PELOD – 2) score as measure of organ dysfunction and pediatric Risk, Injury, Failure, End-stage renal failure (pRIFLE) criteria for acute kidney injury, the number of adverse drug reactions, and re-intubations [27, 28]. We will study the level and time course of the pulmonary and systemic inflammatory response, the prevalence of critical illness polyneuropathy and myopathy, and ventilator-associated pneumonia.

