#### Secondary outcomes

For the secondary outcome measures, repeated measures will be tested using generalised estimating equations (GEE), adjusting for the outcome of randomisation and time and any other confounding factors applicable to the outcome measure. Non-repeated continuous measures will be compared between using either the Student *t* test or the Mann-Whitney *U* test, non-repeated dichotomous variables will be tested using the Chi-squared test or the Fisher Exact test if the absolute value is below 5. They will be displayed as a percentage (%) of the total with a 95% confidence interval.

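### The baseline respiratory score is collected but not pre-specified as a covariate in the primary between-arm model; its only named role for that outcome is a paired comparison that does not estimate the treatment effect

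*Protocol article*

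**What the plan says.** Under Plans for assessment and collection of outcomes {18a}, the primary outcome is a 14-item yes/no parental questionnaire at 12 months, and "The same questionnaire is used upon PICU admission to study baseline respiratory morbidity".

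Three places list the adjustment variables for the primary outcome:

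- The Abstract (Methods) and Outcomes {12} give the same list: age, gestational age, family history, then "season in which questionnaire was filled out, day-care and parental smoking".
- Statistical methods {20a} says "zero inflated regression analysis is used to adjust for possible confounding by age, gestational age, family history of asthma and/or allergy", and continues with season, parental smoking and the parents' perception of the allocation.

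None of the three names the baseline score.

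Statistical methods {20a} mentions the baseline value of the primary outcome once: "Paired analysis will be used to compare the primary outcome with its baseline value". It then adds a conditional rule: "variables that were significantly different between the intervention and control arm will also be adjusted for in the multivariate analysis".

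Outside the primary outcome, the secondary outcome measures include "the level and time course of the cumulative respiratory morbidity score assessed at baseline, 3, 6 and 9 months after PICU discharge", and repeated secondary measures are to be analysed by GEE with terms for randomisation and time.

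**The concern.** The score on the same instrument before treatment is the obvious candidate predictor of the score a year later. In a randomised comparison, adjusting for a prognostic baseline variable removes explained variation from the treatment contrast and corrects for whatever imbalance chance has produced. The trial already plans to collect this variable, so not naming it gives up precision without saving anything.

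The analysis that does use it for the primary outcome answers another question. Comparing a child's 12-month score with the same child's baseline mixes any drug effect with recovery, growth and regression to the mean. The stated aim is between-arm superiority, and this comparison cannot address it.

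**Working it through.** **1. What role the baseline score has.** Setting the sections side by side:

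- Fixed covariates for the primary outcome (Abstract, {12}, {20a}): baseline score not named.
- Paired comparison ({20a}): baseline score used, but the contrast is time, not arm.
- Conditional rule ({20a}): baseline score enters only if it differs significantly between arms. Randomisation makes any such difference a chance event. If the screen is at 5% (the level is not stated), it admits the score in about 5% of trials. The trigger is imbalance, not prognosis, and the final model depends on the data.
- Secondary time course ({12}, {18a}, {20a}): baseline score used together with arm. The time points listed there are baseline, 3, 6 and 9 months, so this does not give a baseline-adjusted estimate of the 12-month primary outcome.

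**2. The plan's sample size.** Inputs from Sample size {14}: independent-sample t test, "assuming a 20% difference in cumulative mean respiratory morbidity score", alpha 5%, power 80%, 74 per arm. No SD or control mean is given, so 74 cannot be reproduced, only back-solved. Assuming a two-sided test:

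d = (1.960 + 0.842) × √(2/74) = 2.802 × 0.1644 = 0.461

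The noncentral t gives 0.464. For a 20% reduction this implies SD/mean = 0.20/0.461 = 0.434. If the 5% were one-sided, d would be 0.409 and SD/mean 0.489.

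**3. Effect of baseline adjustment.** In a linear model the residual variance becomes SD² × (1 − r²), where r is the baseline-to-12-month correlation that remains after the other planned covariates. The protocol gives no r, so the range is an assumption.

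Power at 74 per arm = Φ(2.802/√(1 − r²) − 1.960)

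For example, at r = 0.3: 2.802/√0.91 = 2.937; 2.937 − 1.960 = 0.977; Φ(0.977) = 83.6%. The number per arm for 80% power is 74 × (1 − r²), rounded up.

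| r (assumed) | Variance reduction | Power at 74 per arm | n per arm for 80% |
|---|---|---|---|
| 0 | 0% | 80.0% | 74 |
| 0.1 | 1% | 80.4% | 74 |
| 0.2 | 4% | 81.6% | 72 |
| 0.3 | 9% | 83.6% | 68 |
| 0.4 | 16% | 86.4% | 63 |
| 0.5 | 25% | 89.9% | 56 |

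**4. Does the rule survive a skewed score?** An illustrative simulation used a 0–14 score with an assumed 30% zeros, 74 per arm and a linear model. The adjusted-to-unadjusted variance ratios were 0.97 at r = 0.18, 0.87 at r = 0.32 and 0.71 at r = 0.51. The corresponding values of 1 − r² are 0.97, 0.90 and 0.74, so the approximation is reasonable for a linear analysis of such a score. It was not tested in a zero-inflated model.

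**5. If the paired differences were compared between arms.** With equal variances at the two times, a change score has variance 2(1 − r) relative to the raw 12-month score: 1.6 at r = 0.2, 1.4 at r = 0.3 and 1.0 at r = 0.5. It is less precise than ignoring baseline whenever r is below 0.5, so this reading would not recover the gain.

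**The case against.** A reader might infer more than the text supports, in four ways.

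- *That the baseline score is used nowhere except in the paired test.* It is also part of the secondary time course, in an analysis that includes the randomised arm.
- *That the paired test is run separately in each arm and will be read as improvement in one arm but not the other.* The section does not say it is done by arm and does not rest the efficacy conclusion on it. The between-arm tests are stated separately.
- *That a chance imbalance in the score would go uncorrected.* The conditional rule could correct a significant one. Smaller imbalances would remain, and a significance screen is a poor way to choose covariates, but the score is not excluded outright.
- *That a known amount of power is being lost.* No correlation is given, and it could be low: children under 5 years are eligible, a young infant may have little symptom history to score, and part of any correlation may already be carried by age, gestational age, family history and smoking. At r = 0.1 the gain is 0.4 percentage points.

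Two technical objections also stand. The r² rule is exact only for a linear model. In a zero-inflated model the gain can differ and adding a covariate can change the estimand, so the target effect should be stated. The change is also not entirely free: the trial has been enrolling since May 2019, and amendments go to the ethics committee.

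These points limit the size and certainty of the claim. They do not supply a reason to leave the score out of the named covariates.

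**Conclusion.** The point holds as a missed, low-cost gain in precision. It is not a bias, and it does not invalidate the primary comparison. The baseline score is planned to be collected, is absent from every fixed covariate list for the primary outcome, and is tied to that outcome by name only through a comparison that does not estimate the treatment effect. The significance rule is not an adequate substitute.

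The likely benefit lies between negligible (r around 0.1) and about 10 points of power (r = 0.5). This rests on an assumed r, a standardised difference back-solved under a two-sided 5% test, and a linear-model approximation. The figures start from the planned 80%. If the other covariates explain variation too, the starting and final power are both higher. The asymmetry favours adjustment: little is lost if r is small, and the gain is material if r is moderate.

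**What to change.** In Statistical methods {20a}, and in the matching lists in the Abstract and Outcomes {12}, name the baseline respiratory morbidity score as a covariate in the primary between-arm model regardless of observed imbalance. State whether it enters one or both parts of the zero-inflated model. Add a simple rule for missing baseline values, such as a missing indicator or mean imputation. Label the paired comparison with baseline as descriptive, or delete it.

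The cost is one or two model parameters with about 148 evaluable patients, and an amendment or analysis-plan entry dated before unblinding. No new data are needed.

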Critical care practitioners have adopted the philosophy of maintaining spontaneous breathing in mechanically ventilated patients as much as possible. However, a study in adults with severe ARDS challenged these practices. Early use of neuromuscular blocking agents (NMBAs) in adults with severe ARDS, defined as PaO_2_/FiO_2_ ratio less than 150 mmHg, resulted in improved 90-day survival and increased time off the ventilator without increasing muscle weakness [6]. In this study, 340 patients with early severe ARDS, meeting criteria within 48 h of ICU admission, were randomised to cisatracurium besylate or placebo once adequately sedated. After adjustment for baseline PaO_2_/FiO_2_, plateau pressure and the Simplified Acute Physiology Score, the cisatracurium group had a hazard ratio for death at 90 days of 0.68, (95% confidence interval [CI], 0.48 to 0.98; *P* = 0.04), compared to the placebo group. These findings remained consistent when combined in a meta-analysis with earlier, smaller studies from the same group of investigators [7]. Additional beneficial effects of NMBAs observed included sustained improvement in oxygenation, less organ dysfunction, and a lower pro-inflammatory response [8–10]. However, the practice change that followed this trial came under scrutiny after the publication of the Re-evaluation Of Systemic Early Neuromuscular Blockade (ROSE) trial in 2019 [11]. This trial was designed to determine the safety and efficacy of early NMBAs with concomitant heavy sedation as compared with a strategy of usual care with lighter sedation targets. It was prematurely terminated for futility after the inclusion of 1006 patients because no difference in 90-day survival (42·5% vs 42·8%) was found.

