### Eligibility criteria {10}

Eligible for inclusion are children younger than 5 years of age (< 20kg) with an indwelling arterial/venous catheter in situ, requiring invasive MV with positive end-expiratory pressure (PEEP) ≥ 5 cm H_2_O for moderate-to-severe PARDS occurring within the first 96 h of PICU admission. Moderate-to-severe PARDS is defined by acute onset of disease, oxygenation index (OI) > 12/oxygen saturation index (OSI) > 9.9, one or more infiltrates on chest radiograph and no evidence of left ventricular failure or fluid overload.

Exclusion criteria are:
Known allergy or intolerance to rocuroniumContinuous administration of neuromuscular blockade prior to meeting PARDS criteria/start of studyBolus administration of neuromuscular blockade within 1 h before meeting PARDS criteria/start of studyChronic respiratory failure on home ventilationIntracranial hypertensionPre-existing pulmonary hypertensionCongenital heart disease with left-to-right shunting(Suspected) underlying neuromuscular or metabolic disordersBone marrow transplantationExpected duration of MV less than 48 hWithdrawal of life-sustaining treatment or other treatment limitations

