## Discussion

This is the first paediatric trial evaluating the effects of muscular paralysis in moderate-to-severe PARDS. The proposed study addresses a huge research gap identified by PALICC by evaluating a practical need regarding the treatment of PARDS [39]. Paediatric critical care practitioners are inclined to use interventions such as NMBAs in the most critically ill. Data from the Paediatric ARDS International Epidemiology (PARDIE) study showed that approximately one of every three mechanically ventilated PICU patients received continuous NMBAs [13]. The use of NMBAs increased with PARDS severity and was more common among patients who also received inhaled nitric oxide (iNO) and HFOV. However, this liberal use of NMBAs must be weighed against potential side-effects, with CIPNM being the most prominent, a phenomenon that has been observed especially in adults who are on concurrent corticosteroids or have renal failure [19, 20]. The proposed study will provide much needed scientific support in the decision-making to start NMBAs in moderate-to-severe PARDS.

The primary outcome of this proposed study is a functional one, measured during follow-up. We choose this outcome for two reasons. First, based on the relatively low but highly variable PARDS mortality rates, the proposed study would require a large sample size. Consequently, such a study would have to run for many years, thereby potentially making the study not only not feasible but also creating the risk of the research question becoming less important [1]. Second, the focus in paediatric critical care research is redirecting towards functional outcomes [40, 41]. We think that this makes our primary outcome measure highly relevant. The maximum level of pulmonary function reached during childhood is a crucial determinant for respiratory function in adults [42–45]. Any event that causes lung injury and thereby reduces the level of pulmonary function may thus exert a negative impact on later life. This may especially be true for lung injurious events during early childhood (i.e., children < 8 years of age) when the lung is still developing. MV needs to be considered such an event in our perspective, which makes pulmonary function an important outcome measure.

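### The primary model names no measure of lung-injury severity at entry and admits one only if it differs significantly between arms: a cheaply mended weakness of efficiency and prespecification, not a bias

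*Protocol article*

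**What the plan says.** The covariates of the adjusted primary analysis are stated in two main places.

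- Protocol article, Primary outcome measure: the score is "adjusted for confounding by age, gestational age, family history of asthma and/or allergy, season in which questionnaire was filled out, day-care and parental smoking". The abstract gives the same list.
- Protocol article, Statistical methods for primary and secondary outcomes {20a}: "zero inflated regression analysis is used to adjust for possible confounding by age, gestational age, family history of asthma and/or allergy", continuing with "season in which questionnaire was filled out, parental smoking, and parental perception of the outcome of randomisation". This list drops day-care and adds parental perception.

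Neither list contains OI, OSI or any other measure of how ill the child was at entry.

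Section {20a} then adds two conditional rules. One says that "variables that were significantly different between the intervention and control arm will also be adjusted for in the multivariate analysis". The other says that "we will adjust if there is an imbalance in the use of (non-) pulmonary specific ancillary treatment used during PICU admission". The first could bring entry severity into the model. The second concerns treatment given after randomisation, not severity at entry.

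Eligibility criteria {10} define moderate-to-severe disease partly by "oxygenation index (OI) > 12/oxygen saturation index (OSI) > 9.9", so a qualifying index exists for every enrolled child. Sequence generation {16a} describes blocks of four and mentions no stratification by severity.

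**The concern.** The named covariates are general risk factors for respiratory symptoms in young children. None describes the condition that brought the child into the trial. The protocol's own reasoning makes severity a natural candidate. Its Discussion defends the primary outcome on the ground that "Any event that causes lung injury and thereby reduces the level of pulmonary function may thus exert a negative impact on later life". Its Background reports that the adult trial's survival result was adjusted for baseline oxygenation, "plateau pressure and the Simplified Acute Physiology Score".

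Two things are at stake. If entry severity predicts the 12-month score, omitting it leaves explainable variance in the error term of a trial planned at only 80% power. And leaving its inclusion to a baseline significance test means that the form of the primary model is settled by the trial's own data, while imbalances that fall short of significance go uncorrected.

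**Working it through.** **Inputs from the protocol (Sample size {14}).** 74 evaluable children per arm, alpha 5%, power 80%, independent-samples t test, 20% difference in mean score.

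**Assumptions.** Two-sided alpha; a 5% level for the baseline test, since the rule states none; a linear model with a normal outcome, which only approximates the zero-inflated model; and r, the correlation of entry severity with the 12-month score. The protocol gives no value for r, so a range is shown.

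**1. The plan's own figure.** No mean or SD is given, so 74 per arm cannot be reproduced forwards, only solved backwards:

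d = √[2 × (1.960 + 0.842)² / 74] = 0.461 SD (0.464 with the t distribution).

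A 20% difference equal to 0.461 SD implies an SD of 0.20 / 0.461 = 0.43 of the control mean.

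**2. Precision if severity is always in the model.** The residual SD is multiplied by √(1 − r²), so power = Φ(d/√(1 − r²) × √(74/2) − 1.96). The number per arm giving the original 80% is 74 × (1 − r²), rounded up.

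| r (assumed) | SE ratio | Power at 74 per arm | Equivalent n per arm |
|---|---|---|---|
| 0.1 | 0.995 | 80.4% | 74 |
| 0.2 | 0.980 | 81.6% | 72 |
| 0.3 | 0.954 | 83.6% | 68 |
| 0.4 | 0.917 | 86.4% | 63 |

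Worked line for r = 0.3: 0.461 × √37 = 2.80; 2.80 / 0.954 = 2.94; 2.94 − 1.96 = 0.98; Φ(0.98) = 83.6%.

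**3. What the conditional rule recovers.** 20,000 trials of 74 per arm were simulated, adjusting for severity only when its baseline difference was significant at 5%. The rule was triggered in 5.1% of trials.

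| r (assumed) | Power, never adjust | Power, plan's rule | Power, always adjust | Type I error, plan's rule |
|---|---|---|---|---|
| 0.1 | 80.6% | 80.6% | 80.7% | 5.0% |
| 0.3 | 79.8% | 80.2% | 83.1% | 4.7% |
| 0.5 | 79.6% | 80.8% | 89.4% | 4.1% |

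The rule performs almost like no adjustment, and its type I error does not exceed 5%. (The simulated 83.1% and the formula's 83.6% at r = 0.3 differ through simulation error and the approximation.)

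**4. Imbalance that the rule leaves in place.** The SD of a chance imbalance is √(2/74) = 0.164 severity SDs. The largest non-significant imbalance is about 1.96 × 0.164 = 0.32. The resulting shift, as a share of the target effect, is r × imbalance / d:

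- r = 0.1: 0.1 × 0.322 / 0.461 = 7%, or 1.4 points of the 20% reduction.
- r = 0.3: 0.3 × 0.322 / 0.461 = 21%, or 4.2 points.

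These are the extremes. An imbalance of one SD (0.164) gives 3.6% at r = 0.1 and 10.7% at r = 0.3.

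**The case against.** The strongest reply is that section {20a} already deals with imbalance: the sentence after the covariate list would bring in OI or OSI if the arms differed significantly on it. That stands. A reader might infer from the covariate list alone that any severity imbalance stays in the primary estimate; the text does not support that, because only a non-significant imbalance stays. It does not rescue precision, though, as step 3 shows.

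Second, the sample size rests on an unadjusted t test, so the planned 80% never depended on a severity covariate. This also stands: what is forgone is an available gain, not power that the plan had counted on.

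Third, the documents do not show that entry severity predicts this outcome. The Discussion speaks of having a lung-injuring event, which every enrolled child has had, not of a gradient by OI. The adult trial adjusted 90-day mortality, not parent-reported symptoms at one year. The entry threshold also narrows the severity range. All this is fair, and is why low values of r belong in the range.

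Fourth, a statistical analysis plan that is not shown might add the term. But the article sets out the covariates in the abstract, the outcome section and the methods section, and fixes the rule for adding others, so the point concerns what is stated rather than detail left out.

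A reader might also extend the criticism to ventilator-free days and mortality. The Objectives and the exploratory outcome section class these as exploratory (only the abstract calls them secondary), and unadjusted tests between randomised groups are valid. That extension is a preference, not a fault.

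**Conclusion.** The point holds as a weakness of efficiency and prespecification. The plan names its covariates, leaves out a severity measure that every child has at entry, and lets it in only through a significance test that chance triggers in about one trial in twenty.

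It is tempting to read this as a biased primary result or an inflated false-positive rate. Neither follows: randomisation keeps the comparison unbiased, and simulated type I error under the plan's rule is 4.1% to 5.0%.

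The size is uncertain because r is assumed throughout. The power gain is under 2 points for r of 0.1 to 0.2, about 3.6 points at 0.3 and about 6.4 at 0.4. The 21% shift combines r = 0.3 with the largest imbalance that the rule leaves alone, so it is a worst case at that r. That the covariate is absent and the rule a poor substitute is clear from the text; how much is gained by mending it is not.

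**What to change.** Before unblinding, name entry severity as a fixed covariate in the primary model: the log of the last qualifying OI or OSI before randomisation, with an indicator for which index was used. The indicator is needed because the two indices are on different scales and the choice depends on whether there is an arterial line. The time point should be stated because parents may take up to 12 hours to decide on consent. For this variable, the fixed term should replace the significance-triggered rule, so that its inclusion does not depend on any baseline test. The same term may be used in a supporting analysis of ventilator-free days and mortality, but this is optional.

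The cost is a sentence or two in the analysis plan and no new measurements. The model gains two parameters per component, so up to four in a zero-inflated model. If severity is only weakly prognostic, the gain will be small.
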